## Abstract

**Background:**

People with mental illness are more likely to suffer physical health problems than comparable populations who do not have mental illness. There is evidence to suggest that exercise, as well has having obvious physical benefits, also has positive effects on mental health. There is a distinct paucity of research testing its effects on young people seeking help for mental health issues. Additionally, it is generally found that compliance with prescribed exercise programmes is low. As such, encouraging young people to exercise at levels recommended by national guidelines may be unrealistic considering their struggle with mental health difficulties. It is proposed that an exercise intervention tailored to young people's preferred intensity may improve mental health outcomes, overall quality of life, and reduce exercise attrition rates.

**Methods/Design:**

A sequential mixed methods design will be utilised to assess the effectiveness of an individually tailored exercise programme on the mental health outcomes of young people with depression. The mixed methods design incorporates a Randomised Controlled Trial (RCT), focus groups and interviews and an economic evaluation. *Participants: *158 young people (14-17 years) recruited from primary care and voluntary services randomly allocated to either the intervention group or control group. *Intervention group*: Participants will undertake a 12 week exercise programme of 12 × 60 minutes of preferred intensity aerobic exercise receiving motivational coaching and support throughout. Participants will also be invited to attend focus groups and 1-1 interviews following completion of the exercise programme to illicit potential barriers facilitators to participation. *Control group*: Participants will receive treatment as usual. *Primary Outcome measure*: Depression using the Children's Depression Inventory 2 (CDI-2). *Secondary Outcome measures*: Quality of Life (EQ-5D), physical fitness (Borg RPE scale, heart rate), incidents of self-harm, treatment received and compliance with treatment, and the cost effectiveness of the intervention. Outcome measures will be taken at baseline, post intervention and 6 month follow up.

**Discussion:**

The results of this study will inform policy makers of the effectiveness of preferred intensity exercise on the mental health outcomes of young people with depression, the acceptability of such an intervention to this population and its cost effectiveness.

**Trial Registration:**

ClinicalTrials.gov: NCT01474837

## Background

The Department of Health in England has identified that people who use mental health services, in particular those with diagnosis of schizophrenia or bipolar disorder, are at increased risk of coronary heart disease, diabetes, infections, respiratory disease and greater levels of obesity [1]. Additionally, it is reported that they are almost twice as likely to die from coronary heart disease and up to four times as likely to die from respiratory disorder as those in the general population [2,3]. Consequently, the Department of Health launched a national initiative to improve the physical health of people with mental illness with an aim to promote activity for all [4].

The numerous physical benefits of exercise have been well evidenced throughout the years and are abundant in health promotion literature in G.P surgerys, leisure centres and gymnasiums. Engaging in exercise is associated with reducing the risk of developing heart disease, stroke, cancer, type 2 diabetes and obesity and promoting musculoskeletal health [4]. It improves the poor physical health that leads to morbidity and early deaths in mentally ill populations.

There is a breadth of evidence suggesting that exercise also has positive effects on mental health. Generally it has been found that exercise can have a positive impact on mood, self esteem and self worth [5]. Importantly, it has also been shown to be effective at reducing symptoms of depression and anxiety, this has been evidenced in both the general population [6-8] and in adult clinical populations [9,10]. Although the evidence is scarce there are some studies investigating the association of exercise on mental health, in particular on depression in young people.

Drawing on evidence from a national school based study looking into depression and suicidal ideation of adolescents it was found that higher levels of depression were associated with lower levels of sport participation. After controlling for covariates it was reported that participation in sports reduced the odds of suffering from depression by 25% [11]. Similar reports have been found from longitudinal data; in a 6 Year study of 496 adolescent students, in which assessments of physical activity and depression scores were taken at 1-year intervals, baseline physical activity predicted fewer depressive symptoms over time [12]. This finding is supported by longitudinal studies [13,14].

Experimental data is scarce in the literature and results are mixed; In an RCT comparing participants receiving 24 sessions of aerobic activities of moderate intensity compared to a light contact placebo group and a non-treatment control group, participants in the intervention group improved on measures of self-esteem relative to the control group, however no differences were shown on depression scores [15]. Conversely, in an RCT in which 66 Hispanic students were randomised to an intervention group consisting of moderate intensity aerobic exercise or a control group of low intensity physical activity over a 6 week period, depression scores were significantly lower post intervention in the intervention group [16].

Although there are a wealth of studies testing the association between exercise and mental health in young people in the general population, there is little data on its association in clinical populations, i.e. those seeking treatment for mental health issues. In a systematic review of clinical trials up to 2005 [17] only three trials were found to have investigated the effect of exercise on this population [18-20]. All three studies reported no significant difference between depression scores in the intervention and control groups. However, two of the studies were reported to be of low quality and one was rated as moderate; all three studies had relatively small sample sizes. More recently there have been two studies investigating the effects of exercise on young people in a clinical population with slightly more positive results. In a single measures design study, 15 female participants meeting the Diagnostic & Statistical Manual for Mental Disorders IV (DSM-IV) criteria for Post-Traumatic Stress Disorder (PTSD) undertook an aerobic exercise programme for 40 minutes 3 times a week for12 weeks. Significant reduction in depression scores were reported from baseline to mid intervention and post intervention. However, a significant increase in depression scores was reported at 1 month follow up when comparing post intervention to 1 month. The authors conclude that aerobic training may be an effective intervention for childhood PTSD symptom reduction. However, increase in depression scores at 1 month follow up suggests that reduction in depression is not maintained when exercise ceases [21]. Another single case repeated measures study using 12 female participants (aged 14-17) receiving treatment from a PTSD treatment centre in which participants undertook 25 minute sessions of moderate intensity aerobic exercise 3 times a week for 5 weeks reported that 2 of the 8 participants who demonstrated stable depression scores at baseline showed significant reduction in depression scores post intervention. Importantly, both studies had inadequate sample sizes and no control group and one had a large variance in the type of physical activity participants undertook.

In summary, it is clear that there is potential for exercise to have an effect on depression scores in young adults with depression, however to the authors' best knowledge there has been no well designed RCT's with sufficient statistical power investigating this issue. Furthermore, it is felt that encouraging young people to exercise at levels recommended by national guidelines, or as prescribed by the researcher may be unrealistic for young people with mental health difficulties. The researchers' previous work among young people suggests that interventions tailored to young people's preferred intensity may improve their motivation for exercise and reduce attrition rates and lead to improved mental health outcomes, increase self-esteem and overall quality of life. Therefore, a specially designed programme with exercise at a preferred intensity has the potential to improve health outcomes in young people.

### Objectives

1. To determine the effectiveness of a preferred intensity exercise programme on the mental health outcomes of young people with depression.

2. To examine the acceptability of a preferred intensity exercise programme to young people with depression

3. To determine the cost effectiveness of a preferred intensity exercise programme for young people with depression.

### Hypothesis

It is hypothesised that exercise of preferred intensity will significantly lower depression scores, increase quality of life, reduce incidents of self harm and be more cost-effective than treatment as usual.

## Method/Design

A sequential mixed methods design will be utilised and consists of 3 parts: A Randomised Controlled Trial (RCT), focus groups and interviews, and an economic evaluation. The RCT: Participants will be randomly allocated to preferred intensity aerobic exercise (intervention arm) or treatment as usual (control arm). Outcome measures, which will be collected independently of the research team, will be captured at baseline, post-intervention and six months follow-up. Qualitative data will be collected through face-to-face qualitative interviews and focus groups to understand potential barriers or facilitators to participation. An economic evaluation will also be conducted in order to assess the cost effectiveness of the intervention.

### Sample & recruitment

Participants will be young people aged 14-17 recruited from Primary Care Services, Child and Adolescent Mental Health Services and Voluntary Services in Nottingham City and County in the UK.

The initial approach will be from a member of the patient's usual care team who will be informed about the study. The participants then will be referred by his/her GP/Dr/Health Worker who believes that he/she may benefit from this programme because he/she have been having some difficulties with his/her mental health.

### Inclusion/exclusion criteria

Inclusion Criteria - Young person to be aged between 14-17, receiving treatment for depression or scoring as depressed on the Children's Depression Inventory (CDI)

Exclusion Criteria- participants having any injury or physical health problem or condition that precludes their participation.

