### Screening

Screening will take place by the potential participant's GP or Mental Health Professional who will be given a flow chart of inclusion criteria. Alternatively, if the participant has been referred by non mental health community/voluntary services he/she will be screened by a member of the research team who will administer the Children's Depression Inventory (CDI).

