### Procedure

The intervention group will undertake 12 × 60 minute aerobic exercise sessions, in groups of 5-10, tailored to participants' exercise levels and preferences led by a qualified exercise therapist. The intervention group will also receive psychosocial and motivational support throughout each session to facilitate ongoing participation and enduring change. The motivational coaching will consist of behaviour modification: goal setting, self-monitoring, social support, enhancing self-efficacy and shaping.

Participants will have baseline measures taken at the initial session. Outcome measures will be repeated at post intervention in the final session and at 6 month follow up at a location that suits the participant.

Participants in the intervention group will be invited to participate in focus groups and face-to-face interviews following completion of the exercise programme. These will take place at a location agreed with participants and researchers. It is hoped that these will be conducted at the centres at which the exercise takes place. The data will be recorded on an audio tape with the informed consent from the participants and their legal guardians. The facilitator will also take written notes which will help identify the participants in the recording. Data will be transcribed, coded and analysed for patterns, themes and sub-categories, paying particular attention to outliers and rival explanations given by participants.

The control group will receive usual care throughout the 12 week intervention period. Outcome measures will be taken within the same week as the paired intervention group; at baseline, post intervention (12 weeks later) and at 6 month follow up.

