### Randomisation and blinding

Allocated to experimental or control arm will be by computer generated numbers by a researcher not associated with the study. Measurements of baseline, outcome and follow-up measures will be taken by a researcher not associated with the study. Baseline outcome measures will be taken after random allocation. The exercise therapist and focus group facilitator will only know which participants get the exercise intervention.

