### Statistical analysis

SPSS V.18 will be used for the analysis of the results. The two groups will be described in terms of their baseline characteristics. Our primary outcome will be the CDI post intervention. A regression model will be used to compare the two groups in terms of the CDI score post intervention conditional on baseline score. No other confounders will be adjusted for unless there appears to be an imbalance at baseline between the two groups on pre-specified covariates that are considered to influence outcome. For secondary outcomes, similar models will be built all conditional on the relevant baseline score in addition to baseline CDI score. Analyses will be intention-to-treat and conducted on a dataset where codes for the two intervention groups are unlabeled. All estimates of effect sizes and numbers needed to treat will be reported with 95% confidence intervals. One of the potential problems with early studies testing a relatively new intervention with a group in whom it is largely untested is that the results may be skewed in a positive direction. To minimise this potential effect, the statistical analyses will be conducted independently of the research team. Qualitative analysis of the focus groups and interviews will be conducted using NVivo 9 in order to code the information and look for relevant trends and themes within the data.

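### Treatment for depression at entry can differ between participants and probably predicts the CDI-2, yet the primary model adjusts for such a factor only if an imbalance appears

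*Protocol article*

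**What the plan says.** All references are to the protocol article.

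- **Inclusion/exclusion criteria:** a participant qualifies by "receiving treatment for depression or scoring as depressed on the" CDI. Either condition is enough.
- **Sample & recruitment:** participants are "recruited from Primary Care Services, Child and Adolescent Mental Health Services and Voluntary Services in Nottingham City and County". First contact comes from the usual care team.
- **Screening:** a GP or mental health professional screens most candidates, but "if the participant has been referred by non mental health community/voluntary services he/she will be screened by a member of the research team" using the CDI. Nothing here requires such a candidate to be in treatment.
- **Procedure:** "The control group will receive usual care throughout the 12 week intervention period". What usual care consists of is not described.
- **Randomisation and blinding:** "Allocated to experimental or control arm will be by computer generated numbers by a researcher not associated with the study". No stratification factor is named. Baseline measures are taken after allocation.
- **Statistical analysis:** "A regression model will be used to compare the two groups in terms of the CDI score post intervention conditional on baseline score". Then: "No other confounders will be adjusted for unless there appears to be an imbalance at baseline between the two groups" on covariates specified in advance as likely to influence outcome. The article does not list those covariates.

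**The concern.** The either/or entry rule means that background treatment can differ between participants from the first day. Someone who qualifies through current treatment has, by definition, some depression care as part of usual care. Someone who qualifies on a CDI score alone may have little or none. Background treatment plausibly affects the post-intervention CDI-2, so status at entry is the kind of covariate worth having in the model from the start.

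The stated rule instead makes its inclusion depend on whether an imbalance is seen. This has two drawbacks. The form of the primary model is settled after looking at the data. And a prognostic covariate improves precision whether or not the arms happen to be balanced on it, so waiting for an imbalance gives up part of the gain.

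The second stake is interpretation. The hypothesis and the economic evaluation both compare the programme with treatment as usual. If the effect differs by background treatment, the single estimate depends on the recruitment mix, and a reader cannot tell whether a benefit was seen in treated or in untreated entrants.

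**Working it through.** **Inputs from the article (Sample size and justification):** 128 evaluable, 80% power, SD 16 points, significance level 0.05, 79 recruited per arm.

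**Assumptions, not in the article:** a two-sided test; a target difference of 8 points; an untreated share q of 10% to 50%; a difference in mean CDI-2 between treated and untreated entrants of 4 or 8 points (0.25 or 0.5 SD).

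**1. The plan's own figure.** The target difference is not stated, so 128 cannot be reproduced from the article alone. Solving back from 64 per arm: (1.96 + 0.842) × 16 × √(2/64) = 7.92 points. With 8 points, the normal formula gives 2 × (1.96 + 0.842)² × 16²/8² = 62.8, so 63 per arm (126 in total). The t-test gives 128, with power 80.1%. I therefore use 8 points (0.5 SD).

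**2. Chance imbalance without stratification.** The SD of the arm difference in the untreated (equally, treated) share is √(2q(1−q)/79).
- q = 50%: 0.080, so a 95% range of ±1.96 × 0.080 = ±0.16 (16 percentage points).
- q = 30%: 0.073, so ±0.14.

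The exact (hypergeometric) chance of a difference of 10 points or more is 6.2%, 16.5%, 16.3%, 19.3% and 20.3% for q = 10%, 20%, 30%, 40% and 50%. For 15 points or more it is 0.3% to 5.6%.

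If status is worth 0.5 SD on the CDI-2, the ±0.16 range moves the arm difference by up to about ±0.08 SD (0.078 × 16 = 1.25 points). In SD terms this is 0.5 × 0.080 = 0.040, against a standard error of √(2/79) = 0.159. The ratio squared is about 6% of the variance of the arm difference. That is random error already inside the confidence interval, and conditioning on baseline CDI may absorb part of it.

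**3. Precision gained by always adjusting.** The variance explained by status is q(1−q)m², where m is the mean difference; the residual SD is √(256 − q(1−q)m²).

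| m (points) | q | Variance explained | Residual SD | Power, 64 per arm |
|---|---|---|---|---|
| 4 | 20% | 1.0% | 15.92 | 80.5% |
| 4 | 50% | 1.6% | 15.87 | 80.8% |
| 8 | 20% | 4.0% | 15.68 | 81.7% |
| 8 | 50% | 6.2% | 15.49 | 82.6% |

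**4. Dependence on the mix, if the effect differs.** Suppose, for illustration, 8 points in untreated and 4 in treated entrants. The pooled effect is 8q + 4(1−q): 4.4 at q = 10% and 6.0 at q = 50%. Overall power is then 34% and 56%.

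**5. What effects by status could show.** If 8 points applied in both groups:

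| q untreated | Power, untreated | Power, treated | Power to detect an 8-point difference in effect |
|---|---|---|---|
| 10% | 13% | 76% | 13% |
| 20% | 23% | 71% | 20% |
| 30% | 33% | 65% | 25% |
| 50% | 50% | 50% | 29% |

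At an even split (32 per arm) the 95% half-width within a stratum is about 1.96 × 16 × √(2/32) = 7.8 points, roughly the size of the assumed effect.

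**The case against.** The strongest reply is that this is an ordinary pragmatic trial against usual care. Randomisation draws both arms from the same mix of entrants, so the pooled effect is unbiased for the population recruited, and that is the question the objectives ask. This stands in full.

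A reader might go further and infer that usual care is two different comparators, active treatment for some and next to nothing for others, so that the pooled estimate answers neither question. The article does not support this. It nowhere says that CDI-screened entrants are untreated or will receive no care, and it has the usual care team making first contact. It does not say that usual care is withdrawn in the exercise arm; if it continues there, the contrast is the same for everyone, namely programme added or not. What remains is possible effect modification by background care.

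A reader might also infer that allocation disregards treatment status. The article names no stratification factor, but it condenses a fuller protocol that is not shown, and its silence does not establish that allocation is unstratified. The unlisted covariates may likewise include treatment status. Even so, the stated rule would bring it into the model only on a visible imbalance.

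Finally, the gain is modest and subgroup estimates would be imprecise. Both are true, and they limit what the change can achieve.

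**Conclusion.** The point holds as a modest improvement to a stated analysis rule. Status at entry follows from the eligibility criteria, can be recorded before allocation and is likely to predict the CDI-2, so making its adjustment depend on an observed imbalance is a weak choice. The cost of leaving the rule as it is comprises a small loss of precision (80% power against about 80.5–83%), chance imbalance worth up to about ±0.08 SD, and a result that cannot be read separately for treated and untreated entrants. It does not bias or invalidate the randomised comparison.

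The sizes rest on the assumed 8-point target, two-sided testing, untreated shares of 10–50% and mean differences of 4–8 points by status. The article supplies none of these. The dependence of the pooled effect on the mix arises only if the effect truly differs by status.

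**What to change.** 1. Record whether the young person is in treatment for depression at entry (yes/no) as its own item at screening, before allocation. Do not infer it from referral route: a voluntary-service referral may be in treatment and a GP referral may not. Do not leave it to the baseline assessment, which follows allocation.
2. Include this item as a fixed covariate in the primary regression alongside baseline CDI, whatever the observed balance.
3. Use it as a stratification factor if the full protocol does not already do so.
4. Report the CDI-2 effect with its 95% confidence interval by entry status, labelled as descriptive only.

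**Cost:** one screening item, one model term and one table, plus a second randomisation list if stratification is added. The subgroup estimates will be imprecise: about 50% power in each stratum for 0.5 SD at an even split, and less in the smaller stratum otherwise. They must not be presented as a test of whether the programme works in one group and not the other.
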